### Therapist adherence to study treatment

Therapist adherence to the studied intervention is guaranteed by video-taping each session and video-based supervision.

## Description of control intervention

Patients randomised to the control group receive standard treatment (as usual).

## Concomitant treatment

All patients receive the indicated standard hospital care adapted to their personal needs.

Study participation does not lead to any alteration of the envisaged treatment. However, the following activities are not allowed for participants of both study arms during the trial period:

- additional art therapy,
- visits to art galleries and museums,
- visits to art education seminars,
- creation of pictorial or sculptural works during occupational or other therapies.

## Procedures in case of emergency

In case of an exacerbation of symptoms or severe adverse reactions associated with the study intervention, emergency measures can be taken at any time by the treating psychiatrist, the psychiatrist in charge and senior physicians of the hospital. Symptoms associated with the study intervention may comprise suicidal intention, self-harm, endangerment of others, material damage, increase in psychotic symptoms like desorganisation, delusions, hallucinations, psychomotor agitation or stupor, affective tension, anxiety or perplexity, increase in depressive symptoms, etc.

Should critical situations arise during an art therapy session, nursing staff can immediately assist. The patient may like to finish the session and should be accompanied back to the ward. In case of severe adverse reactions, the intervention has to be discontinued immediately. The treating psychiatrist or psychiatrist in charge will be informed in any case and has to decide about further necessary measures. The treating psychiatrist will also decide about the patient's ability to continue study participation in cooperation with the principal investigator of the study. All adverse and serious adverse events are documented in the case report file and reported to the principal investigator within 24 hours.

## Blinding Procedures

Blinding
Participants, art therapists and supervisors as well as clinical staff involved in the administration of art therapy and practical organisation of the study are aware of allocation status. Clinical ratings are performed by psychiatrists responsible for the study, but not involved in the direct treatment of the participating patients and blind to randomisation. Patients are instructed not to inform the assessor of their allocation status.

Methods of Unblinding and Discontinuation

Unblinding of the psychiatrists responsible for clinical study assessments is only allowed for safety reasons. Regular unblinding of the trial is planned at the end of the trial (last visit, last patient), after closing the database.

# Trial design / plan

see flow chart (chapter 2)

## Trial centre and trial investigator requirements

The Department of Psychiatry, Charité Universitätsmedizin Berlin, comprises two hospitals (Clinic for Psychiatry and Psychotherapy, CCM, [name]) and Psychiatric University Clinic at St. Hedwig Hospital (PUK SHK), [name]). The site is experienced in clinical trials as well as the performance of basic scientific research in the field of schizophrenia. About 600 in- and outpatients with schizophrenia are treated by the trial site quarterly. Experience from previous studies indicates feasibility to recruit a number of 30 patients within 6 months.

## Methods of subject screening and recruitment

The study will recruit patients with schizophrenia during acute psychotic episodes that require hospitalisation. Patients are screened after admission for treatment to one of the general psychiatric wards of the hospital. The population to be screened is based on all patients with schizophrenia referred to the wards (approx. 250 cases/ year, including multiple admissions). These patients are screened observing inclusion and exclusion criteria. As only one intervention group will be run parallel in the pilot study, screening will be stopped after 5 consecutive patients being randomised to the art therapy arm, and re-opened, when treatment places become available.

Accessibility of the intended number of patients: From the approximate number of 250 patients per year it can be assumed that in five months about 100 inpatients with schizophrenia will be treated. A large number of patients of about 70% will meet the inclusion criteria. If about half of them could be expected to agree to study participation, the required number of 30 patients for both study arms will be achieved within the planned recruitment period.

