## Trial Design Overview

The study is planned and performed as a monocentric, randomised controlled pilot study with two parallel groups. The intervention group will be administered 12 sessions of psychodynamic art therapy (twice weekly over 6 weeks, 90 minutes per session), in groups of up to 5 patients, led by a trained art therapist experienced in the treatment of psychoses. The intervention will be aided and each sessions will be video-taped by a trained auxiliary person.

Patients randomisd to the control group will receive treatment as usual (TAU), including all indicated therapy options provided by the study centre. Allocation is open for patients, the art therapist, supervisors and all persons directly involved in the practical execution of the trial.

Psychopathological ratings (SAPS, SANS, CDSS, GAF) are performed by clinicians responsible for the study who are blind to randomisation status. In this pilot study, at least 15 patients will be included into each arm. The total individual trial duration is 12 weeks.

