### Treatment schedule

Patients are treated in groups of up to five people. In the pilot study twelve sessions of art therapy will be performed, offered twice weekly. A session lasts 90 minutes.

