## Methods of obtaining informed consent

After screening for inclusion and exclusion criteria, patients will be informed by their treating psychiatrist about the possibility of study participation at first. This should be preferably done in the first stage of the hospital stay, after completion of the admission procedure and necessary diagnostics and start of treatment. If the patient expresses approval or wishes further information, a psychiatrist responsible for the study will inform her/him about the trial. The information given covers in easily comprehensible terms the aims and organisational features of the study, nature and possible side effects of the intervention, the right to revoke previously given written consent and to withdraw from the study at any time without disadvantage and without having to give an explanation, an offer of more extensive information, the allocation of patients to different treatment groups and randomisation, obligations of the patients and the care-takers, data protection and insurance issues.

Written informed consent is given after a sufficient amount of time to read the Patient Information Form handed over, to discuss the issue with relatives, caregivers and the treating physician and to ask additional questions. If the patient gives informed consent, she/he and the study physician will sign the Informed Consent Form, by which the latter confirms that inclusion criteria are met. Moreover, inclusion and exclusion criteria are confirmed by use of a structured clinical interview for DSM-IV (SCID 1 and 2) [26].

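### Screening closes on an art-therapy allocation, and recruiting and blind rating fall to the same role, so closures can partly unblind the primary-endpoint raters

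*Protocol*

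**What the plan says.** **Closure rule (section 6.2).** The reason given is capacity: "As only one intervention group will be run parallel in the pilot study". The rule follows: "screening will be stopped after 5 consecutive patients being randomised to the art therapy arm, and re-opened, when treatment places become available". Section 5.1.2 sets the capacity: "Patients are treated in groups of up to five people".

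**Who rates (sections 3.1 and 5.5).** "Psychopathological ratings (SAPS, SANS, CDSS, GAF) are performed by clinicians responsible for the study who are blind to randomisation status". Section 5.5 repeats this and adds one restriction: "Clinical ratings are performed by psychiatrists responsible for the study, but not involved in the direct treatment of the participating patients and blind to randomisation". The four scales are the primary endpoints listed in section 3.

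**Who recruits (section 6.3).** The treating psychiatrist makes the first approach. If the patient is interested, "a psychiatrist responsible for the study will inform her/him about the trial". The study physician then signs the consent form and confirms that the inclusion criteria are met. Section 6.2 does not say who does the initial screening.

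**Who knows allocation (section 3.1).** Allocation is open to patients, the art therapist, supervisors and "all persons directly involved in the practical execution of the trial".

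**Safeguards.** Assignment is by telephone from a concealed list held by the central pharmacy, after the baseline examination (section 6.5). Patients are told not to disclose their arm to the assessor (section 5.5). Nothing is said about keeping recruitment status from raters.

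**The concern.** Screening stops because the art-therapy group has just filled, so the stop carries information about the allocation that triggered it. Anyone who recruits has to know whether screening is open, and will usually know who was enrolled last. Raters are barred only from directly treating participants, not from recruiting them. A study psychiatrist who informs patients can therefore learn some allocations from recruitment status alone, whatever the patients say or withhold. Concealment by telephone protects the sequence before assignment. It does not stop a closure from disclosing the assignment just made.

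Patients and therapists are open, so rater blinding is the main protection for four clinician-scored primary endpoints. Baseline ratings precede randomisation, so the exposed ratings are those at weeks 6 and 12, which determine the estimated effect. The protocol intends these effect estimates to inform a larger trial (sections 3 and 13.1), so any rating bias would carry forward.

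**Working it through.** The protocol gives no figure on this point to reproduce. The check asks how many of 30 patients (15 per arm) a rater could place with certainty, under each reading of the closure rule.

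**Inputs from the protocol:** group capacity 5 (5.1.2); one group at a time (6.2); 15 per arm (3.1). **Assumptions:** the rater knows the enrolment order and when screening opens and closes. The list type is not stated, so three were tried by simulation (60,000 sequences each): 15:15 in random order, simple 1:1, and blocks of four. AT is art therapy.

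**(a) Batch refill: close at the fifth AT allocation, reopen for a new group of five.**
- On a 15:15 list there are 15/5 = 3 closures, each revealing its last patient.
- If a batch holds exactly five patients, all five are revealed. The chance per batch is C(25,10)/C(30,15) = 3,268,760/155,117,520 = 0.021.
- Expected number revealed = 3 + 3 × 4 × 0.021 = 3.25, or 10.8% of 30.
- Simulation: 3.25 (10.8%) for 15:15, 2.98 (9.9%) for simple 1:1, 2.83 (9.4%) for blocks of four. Mean closures are 3.00, 2.60 and 2.83.
- Using batch sizes as well, a rater would guess 59% to 65% of arms correctly, against 50% by chance.

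**(b) One place at a time after the first five AT patients.**
- Once the group is full, each reopening is for a single place. An AT allocation closes screening again and a control allocation leaves it open, so every later patient is revealed.
- On a 15:15 list the fifth AT patient falls on average at position 5 × 31/16 = 9.69.
- Expected number revealed = (30 − 9.69) + 1 + 4 × 0.021 = 21.4, or 71.3%.
- Simulation: 21.39 (71.3%), 21.12 (70.4%) and 21.34 (71.1%) for the three list types.

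**(c) Literal reading: five AT allocations in a row.**
- A closure would reveal all five patients in the run.
- The probability of at least one such run is 0.325 (exact) on a 15:15 list, 0.36 with simple 1:1, and 0 with blocks of four.
- This reading does not do what the rule is for: AT allocations separated by a control would not count towards closure, so the group could exceed five.

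**Between (a) and (b).** Suppose places free up as individuals finish an assumed six-week stay, and recruitment runs at the rate in section 6.2: 100 × 0.70 × 0.50 = 35 patients in five months, about 1.6 per week. Simulation then gives about 30% of AT allocations closing screening. That is 0.30 × 15 = 4.5 patients, or 15% of 30, known to be AT from the closure itself.

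**The case against.** **Same role, not shown to be the same person.** A reader might infer that the psychiatrists who screen and obtain consent are the ones who rate. The protocol does not say so. It leaves the screener unnamed, gives the first approach to the treating psychiatrist, and speaks of psychiatrists in the plural. This stands: the point is a shared role label with no separation described.

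**Section 3.1 is not a flat contradiction.** Its next paragraph calls the raters blind, and section 5.5 lists them apart from the staff who know allocation. Read together, raters are probably meant to fall outside the open group. What remains is that someone who informs and enrols patients could reasonably be counted in the practical execution, so the wording needs aligning.

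**Closures do not reveal allocation in general.** A reader might infer that nearly all later allocations become known. That needs strict one-at-a-time refill, which the protocol does not specify. Under it, 11 of 15 AT allocations (73%, the fifth to the fifteenth) would close screening, against about 30% in the simulation at the protocol's own recruitment rate. The 70% is an upper bound.

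**Arm imbalance is a different matter.** A reader might also infer that stopping on AT allocations leaves the control arm short. That would need an unblocked list and recruitment ending at the fifteenth AT patient. Section 3.1 asks for at least 15 in each arm, and the list follows a pharmacy procedure that is not shown.

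**It is a pilot.** True, and only the week 6 and week 12 ratings are exposed. But those ratings supply the effect estimates that are the purpose of the pilot.

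**Conclusion.** The point holds as a partial and avoidable threat to rater blinding. Under the capacity reading, each closure identifies an AT patient to anyone who knows the recruitment status and the last enrolment. The protocol lets the role that informs patients also rate all four primary endpoints, and its instruction to patients not to disclose does not cover this route.

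The certain leak is about 3 of 30 patients (10%) with batch refill and up to about 70% with one-at-a-time refill; the protocol does not say which applies. Both figures assume that raters know the enrolment order and recruitment status. They vary little across the three list types tried. Whether any individual does both tasks for the same patient cannot be settled from the document. The ambiguity of the five-consecutive wording is a separate textual defect in the same sentence, since its literal reading would not hold the group to five places.

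**What to change.** 1. In section 5.5, state that the Visit 2 and Visit 3 ratings of a patient are made by a study psychiatrist who did not inform, consent or enrol that patient.
2. In section 6.2, state that unblinded organisers handle the opening and closing of screening, and that its timing and reason are withheld from raters. Swapping raters without this step would not be enough if every study psychiatrist knows when screening closed and who was enrolled last.
3. In section 6.2, replace the five-consecutive wording with the art-therapy group reaching five occupied places, and say how screening reopens (for a whole new group or for single places).
4. Align sections 3.1, 5.5 and 6.3 so that raters are expressly outside those with open allocation.

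The cost is wording and some scheduling of raters. No extra staff should be needed, because the protocol already provides for more than one study psychiatrist.

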## Methods of obtaining informed consent

After screening for inclusion and exclusion criteria, patients will be informed by their treating psychiatrist about the possibility of study participation at first. This should be preferably done in the first stage of the hospital stay, after completion of the admission procedure and necessary diagnostics and start of treatment. If the patient expresses approval or wishes further information, a psychiatrist responsible for the study will inform her/him about the trial. The information given covers in easily comprehensible terms the aims and organisational features of the study, nature and possible side effects of the intervention, the right to revoke previously given written consent and to withdraw from the study at any time without disadvantage and without having to give an explanation, an offer of more extensive information, the allocation of patients to different treatment groups and randomisation, obligations of the patients and the care-takers, data protection and insurance issues.

Written informed consent is given after a sufficient amount of time to read the Patient Information Form handed over, to discuss the issue with relatives, caregivers and the treating physician and to ask additional questions. If the patient gives informed consent, she/he and the study physician will sign the Informed Consent Form, by which the latter confirms that inclusion criteria are met. Moreover, inclusion and exclusion criteria are confirmed by use of a structured clinical interview for DSM-IV (SCID 1 and 2) [26].

## Methods of avoiding simultaneous enrolment in other trials

Patients are informed that participation in another study at the same time must be reported to the study physician. In inpatients, simultaneous participation in other trials can be easily excluded as the treatment process can be reviewed by study personnel. At the time of the study, no other clinical trials will be conducted at the site. Participation in studies and experiments without intervention of less than 2 days/sessions is possible, if the principal investigator decides that this does not interfere with the course of the KUSS study.

## Methods of assigning subjects to treatment groups (randomisation)

After provision of written informed consent the baseline examination is carried out. Than patients will be randomly assigned to treatment regimens via a randomisation list provided by the central pharmacy of the Charité according to the relevant Standard Operating Procedure. The allocation sequence will be concealed until assignment by telephone.

## Clinical examinations and trial-related deviations of clinical practice

Clinical examinations and symptom ratings, blood tests, pregnancy testing, urine drug screening and ECG belong to necessary routine examinations in schizophrenic patients. Patients with first manifestation of psychotic illness undergo extensive clinical diagnostics including MRI and EEG. Taking a detailed history of the patient and repeated diagnostic interviews also belong to clinical routine. Structured clinical interviews, personality and some of the neuropsychological tests are usually administered according to clinical indication in routine diagnostic procedures. However, the majority of tests and ratings (quality of life, self-efficacy, social cognition) are exclusively performed for scientific purposes. Randomised allocation of treatment is a deviation from clinical practice, the risk of which is minimised by additional visits and standardised ratings of side-effects.

**Table 1:** time schedule for study examinations

| **Instrument** | **Visit 0:**  **Pre-trial** | **Visit 1: Baseline** | **Randomisation**  **and 6 weeks**  **intervention**  **phase** | **Visit 2:**  **Post-treatment**  **(within 7 days after end of intervention)** | **Visit 3: Follow-up**  **(within 7 days after 12 weeks follow-up date)** |
| --- | --- | --- | --- | --- | --- |
| **Informed consent** | x |  |  |  |
| **Inclusion criteria** | x |  |  |  |
| **Demographics** | x |  |  |  |
| **SCID I** | x |  |  |  |
| **SCID II (APD)** | x |  |  |  |
| **SANS/ SAPS** |  | x | x | x |
| **CDSS** |  | x | x | x |
| **GAF** |  | x | x | x |
| **MWT-B** |  | x |  |  |
| **WCST** |  | x |  |  |
| **AVLT** |  | x |  |  |
| **ZUF-8** |  |  | x |  |
| **MSQoL** |  | x | x | x |
| **FKK** |  | x | x | x |
| **RME** |  | x | x |  |
| **LEAS** |  | x | x |  |
| **Medication dose** |  | x | x | x |
| **Documentation of adverse events** |  |  | continuously | x |  |
| SCID I: Structured clinical interview for DSM IV, axis I; SCID II - APS: Structured clinical interview for DSM IV, axis II, screening for antisocial personality disorder; SAPS: Scale for the assesment of positive symptoms; SANS: Scale for the assesment of negative symptoms; CDSS: Calgery Depression Scale for Schizophrenia; GAF: Global Assessment of Functioning; MWT-B: Multiple choice vocabulary test (Mehrfachwahl-Wortschatz-Test); WCST: Wisconsin Card Sorting Test; AVLT: Auditory Verbal Learning Test; FKK: Fragebogen zu Kompetenz- und Kontrollüberzeugungen; ZUF-8: General satisfaction with hospital care (Fragebogen zur Patientenzufriedenheit mit der stationären Behandlung), HAQ: Helping Alliance Questionnaire; MSQoL: Modular System for Quality of Life;  RME: Reading the Mind in the Eyes Test; LEAS: Level of Emotional Awareness Scale. | | | | | |

### Laboratory assessments

Laboratory assessments are not planned in this study.

## Schedule of trial duration, treatment and subject participation

Treatment duration for each individual: 12 weeks

# Risk-Benefit-Analysis

## Risks, side-effects, strains, advantages and disadvantages

Under ethical considerations, the study follows strictly an ‘add-on’ approach. All patients receive the usual standard treatment including pharmacotherapy and any other indicated psychological or adjunctive therapy. The overall amount of adjunctive treatment sessions can be adapted in the control group by participation in additional sessions of occupational or other therapies.

There are no systematic reports on the possible risks and adverse effects of art therapy in general or for its use in the treatment of schizophrenia. In contrast, adverse effects and risks of (group) psychotherapy have been focused increasingly in recent years. Hoffmann et al. 2008 [13] conclude that group dynamic processes may yield negative effects for individual participants. As earls as in the 1960ies, Bergin et al. [13] demonstrated deteriorations of health in about 10% of patients who underwent psychotherapy. According to Margraf et al. [16] three causal categories may be responsible for adverse reactions associated with the psychotherapeutic process:

1. failure or adverse effect of an adequate therapy

2. failure or adverse effect of an inadequate, unprofessionally conducted treatment

3. mismatch between personalities of patient and therapist.

Group therapies might endanger patients if groups are too large, if therapies have a too strongly disclosing/interpreting character and if confrontations between participants are not limited. Also, wrong indication and lack of guidance may increase the risk of adverse reactions [15]. Negative socio-dynamic processes like rivalry, aggression, submission or withdrawal that are not sufficiently contained and resolved by the therapist may have an unfavorable impact on individual patients.

However, despite of potential risks, group therapies are a broadly used and essential means of hospital and outpatient treatment.

In the current study, potential risk for participants must be minimised. Art therapy sessions will be held in small groups. The method itself reduces the probability of interpersonal conflict and confrontation. During the session, the art therapist will successively contact every participant, and thus divide the session in a number of short interaction sequences. Joint reflection of the images is guided by the therapist who safeguards an appreciative and respectful atmosphere. Only qualified art therapists experienced in the treatment of psychotic persons will lead the study sessions.

However, it cannot be excluded that art therapy may cause adverse effects in some participants or the entire group. Emotional processes evoked by this form of therapy may gain greater intensity and lead to destabilisation. In vulnerable individuals this may possibly lead to exacerbation of symptoms, suicidality or aggression. On the other hand it has to be considered that the avoidance of social contact and emotional self-exploration within a professionally led group therapy may have even more deleterious effects on patients. The broad clinical use of art therapy in patients with schizophrenia has given no indication of adverse effects but rather of considerable benefits of this form of treatment.

The remaining risk can be sufficiently controlled within the inpatient setting, permanent professional contact and regular documentation of the patients' condition. All members of staff and study personnel are experienced in the recognition of psychotic crises and the necessary interventions.

Since the expected individual risk is minimal and the expected benefit for the group of schizophrenia patients is high, the overall evaluation of the risk-benefit-ratio is positive.

However, if the occurrence of adverse effects of art therapy was reported, this would be of high clinical interest and consecutively influence routine treatment strategies.

Patients randomised to the art therapy group experience an individual advantage, as psychodynamic art therapy was not offered routinely at the study site in the past. For the same reason, the control group receiving treatment as usual will not be deprived of an indicated therapy. For the whole group of patients with schizophrenia the trial might result in the additional advantage to be offered an evidenced, effective and non-hazardous form of therapy in the future.

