## Trial Duration/Timetable

The trial will be started on January 15, 2011 after a positive vote of the Institutional Review Board (Ethics committee of the Charité University Berlin). From this date, recruitment will take place and is expected to continue until June, 2011. Approximately 30 patients will be included.

The study will be finished after the follow-up phase of the last patient included. Data management and statistical analyses are planned for QIII/IV/2011, the final report for December, 2011.

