### Assessment of Safety

The safety analysis includes all patients with at least one session of art therapy. Safety parameters will be analysed descriptively.

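### The planned safety analysis leaves out the randomised control arm and is descriptive only, so about 15 treated patients could not by themselves support the hope of a non-hazardous therapy

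*Protocol*

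**What the plan says.** Section 2.2 (Rationale) states that evidence on the efficacy and harmlessness of art therapy in psychotic disorders is insufficient. Section 3 then makes preliminary data on efficacy and safety the purpose of the pilot, as preparation for a larger multi-centre trial.

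Section 7.1 looks further ahead. For patients with schizophrenia as a whole, it says that "the trial might result in the additional advantage to be offered an evidenced, effective and non-hazardous form of therapy in the future". The same section states "There are no systematic reports on the possible risks and adverse effects of art therapy" and cites older research that "demonstrated deteriorations of health in about 10% of patients who underwent psychotherapy". It also accepts that adverse effects of art therapy cannot be ruled out.

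Section 13.2.4 is the only safety analysis. Its population is patients with at least one art therapy session, and its method is one sentence: "Safety parameters will be analysed descriptively". Section 3.1 gives the size: "at least 15 patients will be included into each arm". Section 3.2 agrees with this: "Approximately 30 patients will be included".

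Three provisions in section 9 bear on the point. Its opening requires every reported adverse event to enter the analysis. Section 9.1 counts clinically significant worsening of an existing condition as an adverse event. Section 9.6 requires all adverse events during the study to be recorded.

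**The concern.** The harms that section 5.1.1 foresees are worsening psychosis, depression, suicidality and aggression. All of these also occur in the natural course of an acute schizophrenic episode. A count of them among art therapy patients alone says little about art therapy, because some would have happened anyway. The trial has a randomised control group that could supply the missing comparison, and section 13.2.4 defines the safety population so that this group is not in it.

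The second issue is precision. A descriptive listing carries no statement of what the data fail to exclude. If few or no events appear among about 15 patients, a reader who sees the listing beside the section 7.1 wording could take it as more reassuring than it is. At stake are the safety statement in the final report and the safety assumptions taken forward to the larger trial.

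**Working it through.** The protocol gives no safety sample size, margin, bound or power, and section 13.1 says that no sample size estimation was done. There is no planned figure to reproduce.

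**Inputs**
- Treated patients: n = 15 (section 3.1). Dropout is not stated, so 10 to 15 is shown as an assumed range.
- Reference rate: p = 10% (section 7.1). It refers to psychotherapy in general, not to art therapy or acute schizophrenia, and comes without a control rate. It serves only as a yardstick.

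**Upper limit when no event is seen**

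The exact (Clopper-Pearson) limit for 0 of n is 1 − α^(1/n).
- n = 15, one-sided 95%: 1 − 0.05^(1/15) = 18.1%.
- n = 15, two-sided 95%: 1 − 0.025^(1/15) = 21.8%.
- n = 10: 25.9% and 30.8%.
- With 1 event in 15, the two-sided 95% interval is 0.2% to 31.9%.

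A 10% rate is inside all of these. For the two-sided limit to fall below 10% with no events, 1 − 0.025^(1/n) < 0.10 requires n = 36, more than twice the planned arm.

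**Chance of seeing nothing**

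P(0 of n) = (1 − p)^n.
- p = 10%, n = 15: 0.9^15 = 20.6%, so at least one event appears in 79.4% of such trials.
- p = 5%, n = 15: 0.95^15 = 46.3%.
- p = 10%, n = 10: 0.9^10 = 34.9%.

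**What a between-arm comparison could show**
- With no control events, Fisher's exact test at 15 against 15 gives p = 0.100 for 4 treated patients with an event and p = 0.042 for 5. Five of 15 are needed to pass 0.05.
- Fisher power for 20% against 10% is about 4%.

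The control arm therefore supplies the right contrast but not a usable test. That is why an interval is needed, and why a non-significant difference must not be read as safety.

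**The passages side by side**

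Section 9 wants all reported adverse events analysed, whereas section 13.2.4 confines the safety analysis to patients who had art therapy. Events in controls would be recorded under 9.6 and then have no place in the analysis.

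**The case against.** The strongest reply is that nothing in the protocol says absence of events will be interpreted as safety. The section 7.1 sentence is hedged and sits in a risk-benefit discussion. Section 3 calls the data preliminary, and the hypotheses in section 13.2.1 contain no safety claim. All of this stands. A reader might infer that a clean table would be reported as harmlessness and carried into routine care, but the documents do not support that. Section 7.1 says only the converse, that reported adverse effects would influence practice.

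A reader might also take "has given no indication of adverse effects" and "Since the expected individual risk is minimal" as absence of evidence used as proof. That reading is too strong. The judgement of minimal risk also rests on the safeguards described beside it, such as small groups, experienced therapists and inpatient care, and on the exclusion criteria. It is a mitigated-risk judgement and need not be rewritten.

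Nor is individual worsening lost in mean scores, because section 9.1 makes clinically significant worsening an adverse event. A 10% rate would usually show at least one case (79.4%), so going wholly unseen is the less likely outcome.

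Finally, descriptive safety analysis is normal in a pilot, and interval methods are often left to a statistical analysis plan, which is not shown here. The lack of a margin is therefore no error. The safety population is different: section 13.2.4 fixes it explicitly, and it omits the controls.

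**Conclusion.** The point holds in a limited form and is minor. As written, section 13.2.4 yields an uncontrolled event rate in about 15 acutely ill inpatients, which cannot be attributed to art therapy. Even with no event, rates up to about 18% (one-sided 95%) or 22% (two-sided 95%) remain compatible with the data. The pilot alone could not support calling the therapy non-hazardous.

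The bounds assume 15 treated patients and widen if fewer enter the safety set. They do not depend on the 10% figure, which is only a reference value from a different population. The attribution problem holds at any event rate.

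**What to change.** **Section 13.2.4.** Define the safety population as all randomised patients. For each arm, report the number and proportion with any adverse event (including clinically significant worsening as defined in section 9.1) and with any serious adverse event. Give exact 95% confidence intervals and a confidence interval for the difference between arms. The set with at least one session can stay as a supplementary listing. Add that no conclusion of harmlessness is drawn from absence of events or from a non-significant difference. This also reconciles 13.2.4 with the opening of section 9.

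**Section 9.1.** The definition is tied to patients given the intervention. State that the same definition and recording period apply to controls, so that the two proportions are comparable.

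**Section 7.1.** Align the non-hazardous wording with the preliminary aim in section 3.

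A count of patients whose SAPS or CDSS score is simply above baseline at week 6 or 12 should not be added. Two scales at two visits give four chances to be flagged by noise. Assuming normal scores with within-scale correlation 0.5 to 0.7 and cross-scale correlation 0 to 0.3, simulation flags 85 to 89% of patients with no true change.

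**Cost.** One extra table and a few sentences, with no extra visits or patients provided adverse events are recorded alike in both arms. The safety statement will be less favourable, and its intervals will be wide.
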